#### Primary outcome measures

Health Behavior Inventory (HBI): A 20-item questionnaire that assesses concussive symptoms on a 4-point scale, ranging from “never” to “often,” and yields total scores in cognitive and somatic domains. We will use the youth-report version with established reliability and validity in youth with sports injury [37].

Pediatric Quality of Life Inventory (PedsQL): A 23-item questionnaire that assesses physical, emotional, social, and school functioning. The scale includes youth-report and parent-report versions [38–40].

#### Secondary outcome measures

Patient Health Questionnaire (PHQ-9): A 9-item questionnaire that measures the severity of depressive symptoms. Reliability and validity of the PHQ-9 have been established in pediatric populations with injury [41].

Anxiety measures (GAD-7): A 7-item standardized anxiety measure that asks youth to rate how often they have been bothered by anxiety symptoms using a 4-point Likert scale. It has been shown to have good reliability, as well as criterion, construct, factorial, and procedural validity for assessing anxiety [42].

Adolescent Sleep Wake Scale: The 10-item version of the ASWS, including domains of falling asleep, reinitiating sleep, and returning to wakefulness will be used as a measure of sleep quality, based on adolescent report [43].

Daily diary (DD): The 7-day electronic daily diary surveys will include headache, mood, and energy level measures. To assess headache frequency, adolescents will report whether or not they had a headache each day [44] and will rate intensity using an 11-point numerical rating scale (NRS-11) ranging from 0 (“no pain”) to 10 (“worst pain ever”) [45]. These headache frequency and intensity items will be texted and/or emailed in the evening. This electronic 7-day short daily survey has been used successfully to assess headache frequency and pain intensity in prior studies of adolescents [44, 46, 47].

Treatment Evaluation Inventory Short Form (TEI-SF): A 6-item self-report measure that assesses participant perceptions of acceptability and satisfaction with the treatment program on a 5-point scale ranging from “strongly disagree” to “strongly agree.” The TEI-SF has demonstrated adequate reliability and validity across a wide array of treatment studies [48].

Pediatric Inventory for Parents (PIP): The 15-item emotional distress subscale of the PIP will be used to measure the frequency and difficulty of illness-related parenting distress [49].

#### Potential mediators

Parent-Patient Activation Measure (P-PAM): [50]. The 10-item P-PAM will be used to assess parenting self-efficacy in advocacy within the health care system (knowledge, skills, and confidence for managing their child’s health care) [51]. The 4-point scale ranges from “disagree strongly” to “agree strongly” (e.g., “I am confident I can tell a doctor concerns I have about my child’s health”).

Adult Responses to Children’s Symptoms (ARCS): The 13-item Protect Scale and 4-item Monitor Scale from the Adult Responses to Children’s Symptoms (ARCS) [52] measure will be used to assess frequencies of parental protection and monitoring behaviors, with all items rated on a Likert scale ranging from 0 (never) to 4 (always). We adapted this measure to concussion by replacing “pain” with “concussive symptoms,” and it will be given to both adolescent and parent participants.

General Self-Efficacy Scale (GSE): This 10-item scale measures general self-efficacy on a scale of 1 (not at all true) to 4 (exactly true) on items such as “I can usually handle whatever comes my way,” with higher scores indicating greater self-efficacy [53]. Youth will provide self-report on this measure.

### Participant timeline {13}

The participant timeline is shown in Fig. 2.

**Fig. 2 Fig2:**
[figure not shown]
Consort trial flow diagram

### Sample size {14}

We plan to enroll a total of 374 youth-parent dyads across all participating study sites. Three hundred sixty-eight participants will be included in the analyses. The six other participants are considered “training participants,” who will not be randomized and will receive treatment pathway 1 (all intervention components) for the purpose of providing an opportunity for each interventionist to practice intervention delivery with 1–2 families prior to the enrollment of actual study participants. Power analyses were conducted using FactorialPowerPlan SAS Macro for Aims 1 and 3, and PASS for Aim 2 to determine the appropriate number of participants for the study. The factorial design involves 3 completely crossed factors, and thus the same power calculation applies to each factor being tested, and to interaction effects also, since this is a 2^3^ factorial. Based in part on prior investigations by the study team,^1^ assumptions include: 5 assessment points (baseline, 6 weeks, 3 months, 6 months, and 12 months), within-subject correlations over time of *ρ* = 0.6, two-tailed alpha = 0.05, and 10% 12-month attrition were used for all power analyses. In the prior single-site R01 trial, the study team observed 6–12-month HBI treatment effects ranging between 0.26 and 0.32 and PedsQL treatment effects ranging between 0.19 and 0.29. The proposed sample size of 368 (184 per factor present vs. absent comparison) provides power > 0.80 to detect a small effect size of Cohen’s *d* = 0.15 under these assumptions. In terms of the cell size of the factorial design, we will allocate 46 participants to each of the 8 groups and retain an average of 42 participants within each. In terms of power to detect mediation for Aim 2, with “a” the standardized coefficient between the component group and the mediators = 0.34, “b” the standardized coefficient between the mediators and PedsQL/HBI symptom outcomes = 0.34, and with 368 patients, 10% attrition and alpha set at 5%, the power = 0.80 to detect minimal indirect/mediated effect 0.12 [54]. With a total sample size of 368, the component group by moderator interaction effect size was estimated using ANCOVA with baseline HBI or PedsQL as the covariate. With the probability of a 2-tailed type I error set at 5%, the study will have ≥ 0.80 power to detect a component group by moderator interaction ES = 0.25 for 12-month HBI or PedsQL.

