where *Y*_*ij*_ is the outcome for subject *i* at time *j*, *b*_0*i*_ is the subject-specific random intercept to account for within-subject correlation due to repeated measures, and *CHIP*_*i*_ × *Time*_*j*_ is the intervention-by-time interaction term. *CHIP*_*i*_ takes value 1–8 representing each of the 8 combinations of cf-CBT, PS, and CM. *X*_*i*_ is a vector of covariates including baseline injury severity, birth sex, and referring site. We will model *Time*_*j*_ as a discrete variable given a limited number of assessments, the coefficients of the intervention-by-time interaction β_3_ estimate the mean differences between treatment arms in changes (“difference-in-differences”) at later time points relative to baseline. The significance of these coefficients will be assessed using confidence intervals, and *p*-values from *F*-tests based on ANOVA and the Kenward-Roger method [55]. For Aim 1a, we will examine component effects on youth headache, depressive symptoms (PHQ-9) and sleep (ASWS), and parental distress regarding their child’s illness (PIP) using the same methods.

Using our importance criteria, for intervention optimization, we will consider any components or interactions demonstrating an effect size of 0.20 on either the HBI or PedsQL to be worth retaining in the optimized intervention. We will make our initial decision at 6 months, but will also examine 12-month HBI and PedsQL outcomes. We are balancing effectiveness and efficiency in our optimized intervention by not including components that demonstrate a small effect (Cohen’s *d* = 0.20) at 6 or 12 months on the HBI or PedsQL.

#### Aim 2

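### The stated power of more than 0.80 for a component effect of d = 0.15 does not follow from the plan's own inputs; it is about 0.33 to 0.43 at one visit and at most 0.65 to 0.69

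*Protocol article*

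**What the plan says.** The section Sample size {14} lists the inputs for every power calculation: five assessments (baseline, 6 weeks, 3, 6 and 12 months), "within-subject correlations over time of *ρ* = 0.6", and "two-tailed alpha = 0.05, and 10% 12-month attrition were used for all power analyses". Of the cells it says that "we will allocate 46 participants to each of the 8 groups and retain an average of 42 participants within each". From 368 participants, 184 with and 184 without each component, it concludes that the design "provides power > 0.80 to detect a small effect size of Cohen’s *d* = 0.15 under these assumptions". It adds that the same calculation serves every factor and the interactions. Beside this it cites effects from the team's previous trial of 0.26 to 0.32 (HBI) and 0.19 to 0.29 (PedsQL).

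Under Aim 1 in Statistical methods {20a}, the mixed model has a subject random intercept and discrete time, and its intervention-by-time coefficients are differences in change from baseline at each later visit. A component is kept if it shows an effect size of 0.20 on either primary outcome. On timing: "We will make our initial decision at 6 months, but will also examine 12-month HBI and PedsQL outcomes".

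**The concern.** All the inputs are printed next to the result, so the claim can be checked from the document alone. With about 166 to 184 participants on each side, d = 0.15 is a very small difference to detect. Repeated measures correlated at 0.6 help, but only up to a point.

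The figure tells readers that the trial comfortably resolves effects smaller than its own retention threshold of 0.20. If that is untrue at the decision visits, a component that fails to reach significance at 6 or 12 months will be read as stronger evidence against a useful effect than the data can supply.

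**Working it through.** **Inputs.** From Sample size {14}: N = 368 split 184 / 184; 10% loss, so 368 × 0.9 = 331; ρ = 0.6; two-sided alpha 0.05; one baseline and four follow-ups. From Aim 1: a random intercept, a difference-in-change estimand, and decisions at 6 and 12 months. One assumption is added: the correlation is the same between all pairs of visits. This matches the single stated ρ and the random intercept.

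**Formula.** With outcomes in SD units and an equal split, SE(d) = √(4v/N), where v is the variance of the analysed quantity. The effect detectable with 80% power is 2.80 × SE. Power at d = 0.15 comes from the noncentral t; a normal approximation differs by less than 0.005.

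**Variance factors at ρ = 0.6**
- Change from baseline, one visit: v = 2(1 − 0.6) = 0.80
- Baseline-adjusted (ANCOVA), one visit: v = 1 − 0.6² = 0.64
- Mean of four follow-ups minus baseline: v = (1 + 3×0.6)/4 + 1 − 2×0.6 = 0.50
- Mean of four follow-ups, baseline-adjusted: v = (1 + 3×0.6)/4 − 0.6² = 0.34

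**Attempt to reproduce the plan's figure.** For 80% power at d = 0.15, SE must be at most 0.15/2.80 = 0.0535. That requires v ≤ 331 × 0.0535²/4 = 0.237 with attrition, or 368 × 0.0535²/4 = 0.264 without. The smallest v above is 0.34.

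| Contrast | SE, N = 331 | Power at d = 0.15, N = 331 / 368 | Detectable d at 80%, N = 331 / 368 |
|---|---|---|---|
| Single visit, unadjusted (v = 1) | 0.110 | 0.28 / 0.30 | 0.31 / 0.29 |
| Difference in change, one visit | 0.098 | 0.33 / 0.36 | 0.275 / 0.261 |
| ANCOVA, one visit | 0.088 | 0.40 / 0.43 | 0.246 / 0.234 |
| Four-visit mean minus baseline | 0.078 | 0.49 / 0.53 | 0.218 / 0.207 |
| Four-visit mean, baseline-adjusted | 0.064 | 0.65 / 0.69 | 0.180 / 0.170 |

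Using the plan's 42 retained per cell (8 × 42 = 336) instead of 331 gives 0.33, 0.40 and 0.65 for the second, third and last rows. Under equal correlation the last row is also the optimally weighted estimate of a constant effect after baseline, so reweighting the visits cannot improve on it. If the correlation instead decays with lag from 0.6 (AR(1)), the best case falls to 0.54 / 0.59. Linear-slope contrasts give 0.40 to 0.48 with attrition.

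**What would produce 0.80.** Each route departs from the stated inputs:
- Treating the four follow-ups as independent: 0.82 without attrition, 0.78 with it.
- Raising ρ: with attrition, to about 0.77 for the adjusted four-visit mean or 0.88 for single-visit ANCOVA.
- Reading 0.15 as a ±1 effect-coded coefficient or as Cohen's f, either of which equals d = 0.30: unadjusted power 0.82 with 368 and 0.78 with 331.

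**At the plan's own threshold, d = 0.20, N = 331.** The ratios d/SE are 0.20/0.0983 = 2.03, 0.20/0.0879 = 2.27 and 0.20/0.0641 = 3.12. Power is 0.53 (difference in change, one visit), 0.62 (ANCOVA, one visit) and 0.88 (adjusted four-visit mean).

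**The case against.** The strongest defence is that the article condenses a calculation made with a named SAS macro whose settings and effect-size convention are not shown. The 0.15 may be correct on that macro's scale and merely mislabelled. This is possible and cannot be settled here. It does not rescue the sentence, which says Cohen's d and sets 0.15 beside earlier treatment effects of 0.19 to 0.32. Nor does the d = 0.30 reading fully meet the stated inputs, since unadjusted power with attrition is 0.78.

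Second, the 10% is the loss by 12 months, and the mixed model uses everyone with at least one outcome. Applying the full loss to every visit is pessimistic. This stands: a reader might take 0.65 as the ceiling, but the best case lies between 0.65 and 0.69.

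Third, components are retained on an effect size of 0.20, not on significance at 0.15. This also stands. A component with a true d of 0.15 lies below the plan's bar, so missing it is not in itself a failure of the optimisation. The relevant weakness is power at 0.20. That power concerns the significance tests that Aim 1 also plans; it is not the probability that a component is retained.

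Two further inferences are tempting but unsupported. One is that single components realistically have effects of 0.10 to 0.15. That assumes the package effect divides roughly evenly and additively, whereas the Objectives expect components to differ in benefit. The other concerns the moderator statement of "power to detect a component group by moderator interaction ES = 0.25 for 12-month HBI or PedsQL". It lies close to the 0.246 found here for single-visit ANCOVA, but the protocol does not define that effect size, so a numerical match does not establish its scale.

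**Conclusion.** The power statement is wrong as written. At d = 0.15 the stated inputs give 0.33 to 0.36 for the difference in change at one visit, 0.40 to 0.43 for single-visit ANCOVA, and at most 0.65 to 0.69 for the adjusted mean of four follow-ups. At the retention threshold of 0.20, single-visit power with 331 analysed is 0.53 to 0.62.

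This rests on exchangeable correlation at 0.6, Cohen's d in units of the total SD, and no precision gain from covariates other than baseline, since the paragraph states none. To reach 0.80, such covariates would have to remove a further 1 − 0.237/0.34 = 30% of the variance in the best case with attrition (1 − 0.264/0.34 = 22% without).

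Whether the fault is a wrong label or a wrong calculation remains open. A reader might also infer that the trial needs more participants. The point does not go that far: what must change is the stated detectable effect, not the sample size.

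**What to change.** Keep N = 368 and replace the sentence with, for example: *With about 331 analysed, the trial has 80% power for a component main effect of d = 0.25 at 6 or 12 months (baseline-adjusted), 0.28 for the difference in change from baseline at one visit, or 0.17 to 0.18 for the baseline-adjusted average over four follow-ups.*

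Name the contrast to which the headline figure belongs and the scale on which 0.15 was entered in the macro. If it was an effect-coded coefficient or Cohen's f, say so and give the equivalent d. Add the power at d = 0.20 at the 6- and 12-month decision visits. For the moderator figure, define its effect size from the original calculation.

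The cost is one paragraph of wording and a less favourable stated detectable effect. No participants, visits or analyses are added.

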### Recruitment {15}

Recruitment will take place from several sources:

Seattle Children’s Hospital: We will recruit from Sports Medicine, Rehabilitation Medicine, Adolescent Medicine, and Neurology clinics as well as the Emergency Department/Urgent Care within Seattle Children’s Hospital. There will be active recruitment by weekly scanning of the appointment lists for these sites. Providers seeing potentially eligible subjects will be contacted prior to patient visits and asked to provide the patient with study information, including a study flyer and/or a recruitment letter with a QR code that they can scan on their phones and will lead them to the CHIP Study REDCap Screening Form. Clinicians will be provided a dot phrase to share with patients if they would like, explaining the CHIP study. If a patient did not receive study information at their visit, we will send them a recruitment letter, briefly explaining the study and options to contact us, and will then text or call them to assess interest (a maximum of 5 additional attempts). Potential participants will also be provided the link to the study website, https://chipstudy.org. Our website will be public and we are able to recruit participants from anywhere in the USA if they come across the study online and meet eligibility requirements.

University of Texas, Southwestern (Dallas, TX): We will recruit from Sports Medicine, Rehabilitation Medicine, and Neurology providers at UTSW and two other organizations associated with UTSW: Children’s Medical Center and Scottish Rite for Children. The UTSW research assistants will approach patients in person and fill out the CHIP REDCap screening form if they are interested. Seattle Children’s research will take over the recruitment process post-screening form.

#### Assignment of interventions: allocation

##### Sequence generation {16a}

Randomization will occur in blocks according to a computer-generated random assignment and stratified by patient’s sex assigned at birth (male or female) and study site (Seattle, UTSW, or other community). Once the randomization spreadsheet is generated, it will be uploaded into the REDCap randomization module.

##### Concealment mechanism {16b}

Once the randomization spreadsheet is generated by the study statistician, it will be uploaded into REDCap. No one will be able to see the allocation sequence until the “randomize” button in REDCap is clicked and the next participant is assigned to a group.

##### Implementation {16c}

Randomization will occur directly in REDCap by the study coordinator. After randomization, a letter and email will be sent to the participant’s family to notify them of which group they have been randomly assigned.

#### Assignment of interventions: blinding

##### Who will be blinded {17a}

Only the study statistician and fidelity coders will be blinded to the treatment pathways. The data will be coded with a number sequence to indicate the treatment pathways. The research coordinators will have access to the data dictionary with the codes.

##### Procedure for unblinding if needed {17b}

Unblinding of the statistician will only occur after data has been analyzed.

#### Data collection and management

##### Plans for assessment and collection of outcomes {18a}

All outcome data will be collected using self-report surveys in REDCap. Surveys will be completed at 6 weeks and 3, 6, and 12 months after enrollment and will be automatically triggered. See the “Primary outcome measures“ section for detailed descriptions of the measurements.

##### Plans to promote participant retention and complete follow-up {18b}

Research coordinators will be tracking survey completion regularly and reaching out to participants with reminders. Our participant incentive will be tied to their survey completion, to encourage participants to complete surveys on time. Additionally, we will send each of our participants a study gift at 3 months to keep them engaged in the follow-up data collection.

##### Data management {19}

Surveys, video-recorded sessions, and other data will be obtained during the study. Surveys and participant information will be collected and stored in a REDCap project. Video recordings will be stored in a secure Seattle Children’s shared drive.

##### Confidentiality {27}

All study data will be gathered strictly for research purposes and only accessed by study staff. To ensure subject confidentiality, all research surveys and other research materials will be kept in a locked file cabinet in our secure research space, and all computers used in the collection and storage of data will be password-protected or in a HIPAA-compliant database (REDCap). After data is collected, information that would identify the subjects will be removed and code numbers used instead. A study code will be assigned to each subject. Data stored in REDCap will have PHI variables indicated such that a deidentified dataset could be obtained as needed.

##### Plans for collection, laboratory evaluation, and storage of biological specimens for genetic or molecular analysis in this trial/future use {33}

N/A, this study does not collect any biologic specimens.

## Statistical methods

### Statistical methods for primary and secondary outcomes {20a}

#### Aim*** 1***

For Aim 1, the primary purpose of the statistical analyses is to determine whether the three intervention components (a) cf-CBT, (b) PST, and (c) CM each contribute significantly to improvements in post-concussive symptoms (HBI) and youth HRQoL (PedsQL). We hypothesize that over the course of the 12-month trial, families who receive cf-CBT, PS, or CM will demonstrate greater improvements in the primary outcomes compared to those who do not receive these components but that they may be differentially beneficial, suggesting that a streamlined intervention may be comparably effective. To examine this hypothesis, we will perform two sets of analyses. The first set of analyses will examine the effects of individual components (cf-CBT, PST, CM). Towards this end, we will use effect coding of variables for the three components and fit mixed regression models with the following conditional mean structure specification:$$E\left(Y_{ij}\right|b_{0i})=\beta_0+\beta_1cfCBT_i+\beta_2PST_i+\beta_3CM_i+\beta_4Time_j+\beta_5cfCBT\times Time_j+\beta_6PST_i\times Time_j+\beta_7CM_i\times Time_j+\beta_8cfCBT_i\times PST_i+\beta_9cfCBT_iCM_i+\beta_{10}PST_i\times CM_i+other\;interactions+\gamma X_i+b_{0i}$$

where $$cfCBT_i\;=\;1$$  if patient $$i$$ received cfCBT, 0 otherwise, same for PST and CM. The*ot*ℎ*er interactions* include all other two-, three-, and four-way (3 components and time) interaction terms. Based on the mixed models, we can perform repeated ANOVA and test the main effects of each of the three components on our primary outcomes. We will also test for interactions between components.

The second set of analyses will examine the differences across the combinations of the three intervention components as a whole, and identify better-performing combination(s). For this analysis, regardless of linear or generalized linear models, the mean structure for mixed effects regression models can always be specified as

$$(Y_{ij})\;=\;\beta_0\;+\;\beta_1CHIP_i\;+\;\beta_2Time_j\;+\;\beta_3CHIP_i\;\times\;Time_j\;+\gamma X_i\;+b_{0i}$$

where *Y*_*ij*_ is the outcome for subject *i* at time *j*, *b*_0*i*_ is the subject-specific random intercept to account for within-subject correlation due to repeated measures, and *CHIP*_*i*_ × *Time*_*j*_ is the intervention-by-time interaction term. *CHIP*_*i*_ takes value 1–8 representing each of the 8 combinations of cf-CBT, PS, and CM. *X*_*i*_ is a vector of covariates including baseline injury severity, birth sex, and referring site. We will model *Time*_*j*_ as a discrete variable given a limited number of assessments, the coefficients of the intervention-by-time interaction β_3_ estimate the mean differences between treatment arms in changes (“difference-in-differences”) at later time points relative to baseline. The significance of these coefficients will be assessed using confidence intervals, and *p*-values from *F*-tests based on ANOVA and the Kenward-Roger method [55]. For Aim 1a, we will examine component effects on youth headache, depressive symptoms (PHQ-9) and sleep (ASWS), and parental distress regarding their child’s illness (PIP) using the same methods.

Using our importance criteria, for intervention optimization, we will consider any components or interactions demonstrating an effect size of 0.20 on either the HBI or PedsQL to be worth retaining in the optimized intervention. We will make our initial decision at 6 months, but will also examine 12-month HBI and PedsQL outcomes. We are balancing effectiveness and efficiency in our optimized intervention by not including components that demonstrate a small effect (Cohen’s *d* = 0.20) at 6 or 12 months on the HBI or PedsQL.

#### Aim 2

Mediational analyses will account for the temporal associations between treatment group assignment, hypothesized mediators, and the PedsQL and HBI outcomes at 6 months. For the mediational analyses, the component assignment will be the predictor variable. For these analyses, component comparisons of the mediators (youth self-efficacy regarding CBT, parental protectiveness, and parent self-efficacy regarding engaging with health care) will be assessed over the course of the first 6 months post-randomization. We hypothesize that youth receiving cf-CBT will report increased self-efficacy regarding CBT; that parents receiving PST will report decreased parental protectiveness; and that families receiving care management will report higher self-efficacy regarding managing their child’s medical care. The total intervention effect on study outcomes will be parsed into direct and indirect pathways. The study team will fit separate mediational models for the proposed mediators and will use linear regression models for the analyses of mediated data. The regression equations can be schematically depicted as follows, HBI ~ cf-CBT + Covariates,

$$\mathrm{Youth}\;\mathrm{Self}-\mathrm{efficacy}\sim\mathrm{cf}-\mathrm{CBT}+\mathrm{Covariates},$$

$$\mathrm{HBI}\;\sim\;\mathrm{cf}-\mathrm{CBT}\;+\;\mathrm{Youth}\;\mathrm{Self}-\mathrm{efficacy}\;+\mathrm{Covariates}$$

Note the first two equations correspond to cross-sectional analysis for primary and secondary endpoints. The third equation allows us to examine the association between concussion symptoms and self-efficacy in the presence or absence of a cf-CBT program.

Given these model objects, the estimation will proceed by simulating the model parameters based on their approximate asymptotic distribution (i.e., the multivariate normal distribution with the mean equal to the parameter estimates and the variance equal to the asymptotic variance estimate), and then computing causal mediation effects (average causal mediation effect, ACME) of interest for each parameter drawn. This procedure has been implemented in the R {mediation} package [56, 57]. The role of other hypothesized mediators can be assessed using the same approach.

#### Aim 3

Moderator analyses will assess whether each component impacts primary outcomes differentially based on demographic and clinical factors measured at baseline. For demographic factors, we will examine the variables of parental education (4-year college degree vs. less education); youth assigned sex at birth (male or female), and youth race/ethnicity (Hispanic, non-Hispanic white, and non-Hispanic non-white) as moderators. For clinical factors, we will examine youth depression at baseline (PHQ-9 score ≥ 10 vs. < 10) and parent distress (as measured by the PIP, dichotomized based on a median split). To test these exploratory moderators, the study team will first examine the two-way interaction of component groups by each factor measured at baseline. If a significant interaction is detected, the study team will conduct a subgroup analysis and examine each of the component effects using mixed model regression within the subgroup defined by the moderators.

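### The primary model names effect coding but defines the components as 0/1, and fixes no contrast or test type, so it permits either a 184-versus-184 or a 46-versus-46 component effect

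*Protocol article*

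**What the plan says.** The Aim 1 text of the statistical methods section {20a} states the coding twice. Before the equation: "we will use effect coding of variables for the three components and fit mixed regression models". After it, the cf-CBT variable equals 1 if the patient "received cfCBT, 0 otherwise, same for PST and CM". The terms not written out in the equation "include all other two-, three-, and four-way (3 components and time) interaction terms". From this model, the article says, "we can perform repeated ANOVA and test the main effects of each of the three components on our primary outcomes".

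Time is to be modelled "as a discrete variable given a limited number of assessments", with the interaction terms read as changes relative to baseline. This is said of the second Aim 1 model, and I take it to apply to the first as well. The same section judges components and interactions against an effect size of 0.20, initially at 6 months and then at 12 months.

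Sample size {14} rests on "184 per factor present vs. absent comparison", and on the claim that "the same power calculation applies to each factor being tested, and to interaction effects also". On cells it says: "we will allocate 46 participants to each of the 8 groups and retain an average of 42 participants within each".

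**The concern.** Effect coding is sum-to-zero: -1/+1 or -0.5/+0.5. A variable equal to 1 or 0 is dummy coding. In a model without interactions the choice would not matter for the component effects. In a model with all interactions it decides what each lower-order term means. Under sum-to-zero coding a component term averages over the levels of the other two components and uses all eight groups. Under 0/1 coding it is the effect of that component when the other two are absent, and it uses two groups.

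What is at stake is the estimand of the primary analysis. The averaged effect is the one the trial was sized for. The simple effect answers a different question with a quarter of the participants, and the two agree in expectation only if the components do not interact. If the simple effect were also compared with the 0.20 criterion, a noisier estimate would fall on the wrong side of it more often, in either direction.

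**Working it through.** **Inputs.** N = 368 in 8 equal groups, within-subject correlation 0.6, two-tailed alpha 0.05 and 10% attrition (Sample size {14}). Group 4 is cf-CBT only, 6 is PST only, 7 is CM only and 8 is surveys only (Table 1). Outcome SD is set to 1. Equal cells and complete data are assumed unless stated.

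**The plan's own figures.** 368/8 = 46 and 4 × 46 = 184, as stated. 46 × 0.9 = 41.4, stated as 42. The stated power above 0.80 at d = 0.15 does not reproduce if d is the present-minus-absent difference: between-subject analyses give 0.28 to 0.65 after attrition. It is exceeded if 0.15 is a -1/+1 coefficient, that is, a difference of 0.30 (0.86 for a change score, 0.93 for ANCOVA on one post score, after attrition). That is a separate question, and nothing below depends on it.

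**What each term estimates.** Inverting the saturated design matrix (three components, five visits, baseline as the reference visit) gives the weights on the cell means.

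- 0/1 coding, cf-CBT × 6 months: (group 4 at 6 months - group 4 at baseline) - (group 8 at 6 months - group 8 at baseline). The other six groups have weight zero. PST and CM likewise become 6 versus 8 and 7 versus 8.
- Sum-to-zero coding (±0.5), same term: the mean change in the four groups with cf-CBT minus the mean change in the four without.
- The plain cf-CBT coefficient is a baseline difference under either coding: group 4 versus 8, or four groups versus four.

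**Standard errors, 6-month change.** Variance of a change = 2(1 - 0.6) = 0.8.

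- 0/1: √(2 × 0.8/46) = 0.187
- Averaged: √(2 × 0.8/184) = 0.093
- Ratio 2; variance ratio 184/46 = 4.

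**Consequence at the 0.20 criterion, after attrition (41.4 per cell, 165.6 per side).**

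| Analysis | Quantity | Averaged effect | 0/1 coefficient |
|---|---|---|---|
| 6-month change | Power at d = 0.20 | 0.53 | 0.17 |
| 6-month change | Detectable d at 80% power | 0.275 | 0.55 |
| ANCOVA, mean of 4 post scores | Power at d = 0.20 | 0.88 | 0.35 |
| ANCOVA, mean of 4 post scores | Detectable d at 80% power | 0.18 | 0.36 |

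The absolute powers depend on the outcome summary chosen and are not the power of the Aim 1 mixed model. The factor of 2 is common to both rows of detectable effects.

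**Interactions.** Under 0/1 coding a component × component × time term is the interaction in change with the third component absent: four cells, SE √(4 × 0.8/46) = 0.264. Averaged over the third component, the same difference-in-differences has SE √(2 × 0.8/46) = 0.187. As a doubled -1/+1 coefficient, which is half that difference, its SE is 0.187/2 = 0.093, equal to that of a main effect. The equality of power claimed in Sample size {14} therefore belongs to the -1/+1 scale and does not hold for 0/1 coefficients. A term containing all three components is the same contrast under either coding, apart from its scale.

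**Does the choice of test matter?** In one simulated balanced data set, F for a component was 3.04 under effect coding for type I, II and III tests. Under 0/1 coding it was 3.04 for types I and II, but 0.002 for type III and for the coefficient test.

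**The case against.** The strongest reply is that the intent is plain. The article names effect coding, announces ANOVA tests of main effects, and sizes the trial on 184 per side. Those three statements agree, and only the short definition under the equation is out of line. Recoding does not change the fit of a saturated model, and the main effects can be recovered from a 0/1 fit. Test type and contrast details are commonly left to an analysis plan, which is not shown here.

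Most of this stands, and it limits the point. A reader might infer that the primary tests will be 46-versus-46 comparisons and that the efficiency of the factorial design is lost. The article does not support that, because effect coding is also stated and the loss occurs only if raw coefficients, or type III tests on the 0/1 variables, are read. Nor is sum-to-zero coding the only route: marginal contrasts from a 0/1 fit give the same main effects. The article also does not say that lower-order coefficients are what will be compared with 0.20.

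What does not fall away is the contradiction itself. The point is not that a detail is absent. The coding of the primary model is stated twice, incompatibly, and the explicit definition is the one a programmer would implement. Announcing an ANOVA does not settle the matter, since its result depends on the test type.

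**Conclusion.** The inconsistency is real and affects the primary model. Implemented as 0/1 and read from coefficients or type III tests, each component-by-time effect becomes a comparison of one component alone with surveys only, with exactly twice the standard error of the averaged effect when cells are equal. Implemented as effect coding, or through marginal contrasts, the analysis is the one the trial was sized for. The article permits both. The conclusion rests on the full-interaction model as written, equal cells, and discrete time referenced to baseline in the first Aim 1 model. It does not show that the intended analysis is underpowered or that the design is flawed.

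**What to change.** Replace the definition under the first Aim 1 equation with: *cfCBT_i = +0.5 if patient i was assigned to cf-CBT and -0.5 otherwise; same for PST and CM* (or +1/-1, with the coefficient doubled to give the present-minus-absent difference). Alternatively, keep 0/1 and state that main effects are marginal contrasts averaged over the other two components.

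Recoding alone is not enough, because the plain component coefficient remains a baseline difference. Add that the component effect, and the quantity judged against 0.20, is the averaged component-by-time contrast (change from baseline) at 6 months, and at 12 months. Report simple effects only as follow-up to an interaction.

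State the scale for interactions too. With no three-component effect, a difference-in-differences of 0.40 is 0.40 under 0/1 or ±0.5 coding but 0.20 as a doubled -1/+1 coefficient, so the 0.20 criterion has no fixed meaning for interactions until the scale is chosen.

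The cost is a few sentences in the protocol and one line of analysis code. Recruitment, data collection and sample size are untouched. It should be settled before any outcome data are analysed.
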